### Follow-up

During the 12-week follow-up period, trained personnel will contact the participants each week via telephone. Participants will be asked about the KOA and whether they have received other treatments. Participants will be asked to attend a follow-up clinic at 6 and 12 weeks to assess pain, swelling, range of motion, muscle strength, average walking distance, stair climbing ability, activities of daily living (ADL), quality of life (QOL) and medication usage.

### Outcome assessment

Outcome measures have been selected based on those recommended for clinical trials of KOA [27] (Table 6).

**Table 6 T6:** Summary of measures to be collected

**Outcome measures**	**Data collection instrument**
**Primary outcome measures**	
Pain	Visual analogue scale (VAS)
Swelling	Girth measurement
Knee range of motion	Range of motion (ROM)
Muscle strength	Manual muscle test (MMT)
Walking distance	Six-minute walking test (6 MW)
The time to ascend and descend a flight of stairs	Stair-climbing test (SCT)
**Secondary outcomes**	
Pain	Average daily consumption of drugs
Activities of daily living	Modified Barthel index (MBI)
Quality of life	Medical outcomes short form 36 health questionnaire (SF-36)
**Other outcomes**	
Adverse events	Safety assessments
Cost	Economic evaluation

### Primary outcomes

Average knee pain will be self-assessed using a 100 mm visual analogue scale (VAS) with terminal descriptors of ‘no pain’ and ‘worst pain possible’. The VAS pain measurement has demonstrated reliability in KOA [27].

Knee girth will be determined using a flexible plastic measuring tape to measure the transverse plane circumference of the knee at the mid-patellar height, with the patient in a supine position. Girth measurement has shown acceptable reliability for determination of gross changes in knee swelling after knee surgery [28].

The knee’s range of motion (ROM) will be measured using a standard long-arm goniometer. To determine knee flexion ROM, patients will be asked to slide the heel actively towards the buttocks and maximal active knee flexion will be measured. Knee ROM in patients with KOA has been shown to be adequately reliable with a coefficient of 0.96 for flexion and 0.81 for extension [29].

The manual muscle test (MMT) will be performed according to Medical Research Council (MRC) guidelines [30]. The British MRC has developed a muscle scale that grades muscle strength between 0 and 5 [31]. According to the muscle scale, 0 = no palpable contraction, total paralysis; 1 = flicker or trace of muscle contractions; 2 = active movement with gravity eliminated; 3 = full range with gravity eliminated; 3– = partial range against gravity; 3+ = full range against gravity with no resistance possible; 4 = slight resistance; 4– = mild resistance; 4+ = moderate resistance; 5– = barely detectable weakness and 5+ = normal motor power.

Walking performance will be assessed using the six-minute walking test (6 MW). This measures the distance that participants are able to walk in 6 minutes while wearing their usual footwear. Patients will be allowed to use a cane, if necessary. Standardized feedback will be provided to patients during each test as described previously [32]. The 6 MW test will be done twice and the test results averaged. A longer walking distance than baseline will indicate better walking performance. The 6 MW test has excellent test-retest reliability from 0.95 to 0.97 and a low coefficient of variation (10.4%) [33].

The stair-climbing test (SCT) is a physical performance test that measures the time it takes to ascend and descend a flight of stairs. Patients will be asked to complete the test as quickly as they can while still feeling safe and comfortable. Patients will be allowed to use a device if necessary, though participants will be encouraged to perform the test without the aid of a device if possible. Rejeski [34] found that a similar stair-climbing task had an excellent test–retest reliability coefficient of 0.93.

Based on the *Guidelines for the Clinical Research of Chinese Medicine New Drugs* (2002) [35], the curative effect for KOA is calculated as:

$$\begin{array}{l} \mathrm{Curative}\;\mathrm{effect}\\ \;=\left(\mathrm{Total}\;\mathrm{score}\;\mathrm{before}\;\mathrm{treatment}–\mathrm{Total}\;\mathrm{score}\;\mathrm{after}\;\mathrm{treatment}\right)\\ \;\times 100/\mathrm{Total}\;\mathrm{score}\;\mathrm{before}\;\mathrm{treatment} \end{array}$$

where the total score before and after treatment is based on the measures above.

The standard comprehensive effect:

•clinical cure: curative effect ≥ 90%

•obvious effects: 75% ≤ curative effect < 90%

•effective: 35% ≤ curative effect < 75%

•invalid: curative effect < 35%

The efficiency of a treatment is calculated as:

$$\begin{array}{l} \mathrm{Efficiency}\;\left(\%\right)=\left(\mathrm{Number}\;\mathrm{of}\;\mathrm{clinical}\;\mathrm{cures}\right)\\ \;+\mathrm{Number}\;\mathrm{of}\;\mathrm{cases}\;\mathrm{with}\;\mathrm{obvious}\;\mathrm{effects}\\ \;\left(+\mathrm{Number}\;\mathrm{of}\;\mathrm{effective}\;\mathrm{cures}\right)\\ \;\times 100/\mathrm{Total}\;\mathrm{number}\;\mathrm{of}\;\mathrm{cases} \end{array}$$

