### Exclusion criteria

Patients are excluded if they have:

•severe knee swelling

•a muscle strength of grade 2 or below according to a manual muscle test

•a history of trauma to the knees

•serious heart, kidney, liver or nervous system disease, or lower limb gangrene due to diabetes.

•lower limb dysfunction caused by spinal, hip or ankle joint disease, or prior knee joint surgery

•a tumor of the knee joint

•a cognitive or psychological disorder

•received traditional exercise training and/or *tuina* for the knee within the last 4 weeks

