### Experimental group

The experimental group will be treated according to the CTCMRP (Table 2).

**Table 2 T2:** TCM rehabilitation based on syndrome using appropriate technology

**Symptom**	**TCM rehabilitation treatment**
Diagnosis of KOA and inclusion and exclusion criteria	Basic rehabilitation: Chinese medical herb fumigation-washing + traditional exercises (developed from simplified t’ai chi and *yi jinjing*)
Swelling (mild to moderate by knee girth)	Basic rehabilitation + bloodletting by puncturing and cupping
Weak muscle strength (over 3 degrees by MMT)	Basic rehabilitation + *tuina*
Pain (over 5 by VAS)	Basic rehabilitation + acupuncture

In all cases, Chinese medical herb fumigation-washing with traditional exercises (to a basic prescription) will be used. If there is significant swelling in the joint, basic rehabilitation plus cupping and bloodletting will be used. When there is a significant decrease in joint strength, basic rehabilitation plus *tuina* will be used. When there is significant joint pain, basic rehabilitation plus acupuncture will be used.

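### The printed manual muscle test scale, a primary outcome, is not consistently ordered: grade 3 is described as weaker than 3–, so ranking by label can score improvement as worsening

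*Protocol article*

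**What the plan says.** Table 6 of the Protocol article lists muscle strength, measured by "Manual muscle test (MMT"), among the primary outcome measures. The Primary outcomes section says the test follows Medical Research Council (MRC) guidelines, on a scale that "grades muscle strength between 0 and 5", and then prints the grades. Those around grade 3 read:

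- grade 2: "2 = active movement with gravity eliminated"
- grade 3: "3 = full range with gravity eliminated"
- grade 3–: "partial range against gravity"
- grade 3+: "full range against gravity with no resistance possible"

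Grade 4 is then described by slight resistance, 4– by mild and 4+ by moderate.

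The grades are used elsewhere. The Exclusion criteria rule out "a muscle strength of grade 2 or below according to a manual muscle test". Table 2, under Experimental group, has a treatment row headed "Weak muscle strength (over 3 degrees by MMT"). The total score behind the curative effect is based on the primary measures, MMT among them. The Statistical analysis section plans repeated measures ANOVA or a rank-sum test for the primary outcomes.

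**The concern.** Either planned analysis needs grades that rise with strength. As printed, the label with the minus sign, which ordinarily means lower, belongs to the stronger of two neighbouring states. Someone who codes the grades by label would record a gain in strength across that step as a loss. Because patients at grade 2 or lower are excluded, the step lies at the bottom of the eligible range.

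The overlap between grades 2 and 3 raises a second question, because the eligibility boundary falls between those two grades.

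**Working it through.** The article gives no figure for MMT, so there is none to reproduce. The check compares the order of the labels with the order of the descriptions.

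**Inputs.** Eleven grades are printed, in this sequence: 0, 1, 2, 3, 3–, 3+, 4, 4–, 4+, 5–, 5+. The usual label order puts x– below x and x below x+.

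**Pairs.** Eleven grades give 11 × 10 / 2 = 55 pairs. In two of them the label order is opposite to the printed sequence: (3, 3–) and (4, 4–).

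**Pair 3 and 3–.** Grade 3 needs no movement against gravity, and 3– needs some. By description 3– is stronger; by label it is weaker. This is a clear inversion within the text, and no outside source is needed to see it. The printed sequence does rise in strength here (3, then 3–, then 3+). The label is what is out of place.

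**Pair 4 and 4–.** Slight and mild are close to synonyms. Either the two grades cannot be told apart, or, if mild means more than slight, the labels are inverted here too. The wording does not settle it.

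**Grades 2 and 3.** Full range without gravity is also active movement without gravity, so a patient in that state meets both definitions. Graded 2, the patient is excluded; graded 3, the patient is eligible.

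**Effect of the coding choice.** Number the 11 grades 1 to 11, once by label and once by printed position:

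| Grade | Rank by label | Rank by position |
|---|---|---|
| 3– | 4 | 5 |
| 3 | 5 | 4 |
| 3+ | 6 | 6 |

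- Change from 3 to 3– (stronger, as described): by label 4 − 5 = −1; by position 5 − 4 = +1. The sign flips.
- Change from 3 to 3+: by label 6 − 5 = +1; by position 6 − 4 = +2. Same sign, different size.
- Change from 3– to 3+: by label 6 − 4 = +2; by position 6 − 5 = +1. Same sign, different size.

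Only movement between 3 and 3– changes direction, in either sense, together with movement between 4 and 4– if that pair is also inverted.

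**Table 2.** By label, 3– is not above 3; by description it is. Which patients meet that row's MMT condition therefore depends on the reading.

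**The case against.** The strongest reply is that the harm depends on a coding rule the article does not contain. Scoring by printed position would avoid the inversion at grade 3, and numeric coding is commonly left to an assessor manual or analysis plan. This stands, and it makes the consequence conditional. It does not remove the defect: the article does not say to code by position, and different coders could treat 3 and 3– in opposite ways.

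Second, the test is said to follow a cited guideline, so the list may be a loose paraphrase that assessors never used. This also stands as a possibility. Nothing in the article shows which sheet was used, and nothing in it corrects the list.

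Third, few patients may be affected. Participants have early- to middle-stage disease and are tested on walking and stair climbing, so a patient with no movement against gravity in the tested muscle may be rare. That is plausible, but it is an inference, since no grade distribution is given.

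A reader might infer that every patient who improves across the step will be counted in the wrong direction, or that the curative-effect result is distorted. The document supports neither. The first holds only under label ranking, and how MMT enters the total score is not stated. A reader might also object to the missing plain grade 5 and the 5+ label, but 5– lies below 5+ both by label and by description, so the order is not disturbed there.

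**Conclusion.** The printed scale for a primary outcome is internally inconsistent. One pair (3 and 3–) is clearly inverted, one (4 and 4–) cannot be ordered from its wording, and grade 3 overlaps grade 2 at the eligibility boundary. If grades are ranked by label, a real gain from 3 to 3– is scored as a loss of one rank.

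The size of the effect on the trial's result cannot be computed, because the share of patients at these grades is not given; it may be small. The sample size rests on curative-effect rates and does not change. The conclusion assumes only that moving against gravity takes more strength than moving without it, and that a minus sign is read in the usual way. Whether the list matches the cited guideline was not judged. This is an error in an outcome definition that is worth correcting; the document does not show that the primary analysis is wrong.

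**What to change.** 1. Replace the list with one strictly ordered set of grade descriptions, checked against the guideline the trial cites, so that adjacent grades neither overlap nor share a meaning.
2. Fix one numeric rank per grade for analysis, before unblinding.
3. For grades already recorded, first establish which grading sheet the assessors used, and map to the corrected ranks only on that basis. Blanket recoding by the printed descriptions should be avoided: if assessors graded from the guideline, it could misorder grades that were recorded correctly, and if only labels were recorded there is no description to recode from.
4. Reconcile the MMT grade references in the Exclusion criteria and in Table 2 with the corrected list. Which clinical cut-off is intended is for the investigators to state.

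The cost is one corrected paragraph, a corrected assessor sheet if the printed list was in use, a short coding rule, and a check of the grades already recorded. Recruitment is reported as ongoing, so later assessments can still use the corrected list.

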### Secondary outcomes

The average daily consumption of non-steroidal, anti-inflammatory drugs.

ADL performance will be assessed using the modified Barthel index (MBI) [36], which is based on 10 items and is scored on a scale from 0 to 100. A higher score indicates more independence [37].

QOL will be evaluated using the medical outcomes short form 36 health questionnaire (SF-36). The SF-36 has been found to be reliable and is easy to administer [38-40]. The questionnaire has eight scales for different domains of health as follows: physical functioning, bodily pain, physical state, general health, vitality, emotional state, social functioning and mental health. Each scale is scored between 0 and 100 with 100 representing the best score possible. The PCS (physical component scales, summary scales of physical functioning, bodily pain, role-physical and general health) in SF-36 will be the main focus of this investigation as it is a composite of all scales representing the physical aspects of health.

### Safety assessments

Trial coordinators and therapists at each CHC will record adverse events and the details of these events, throughout the study and during the follow-up period. Participants will be able to report adverse events at any time during the trial and will receive advice accordingly. Serious adverse events will be reported to the Human Research Ethics Committee (HREC) of FJTCM.

### Economic evaluation

The cost of interventions will be assessed during the rehabilitation period, including the length of any hospital stay, emergency department visits, general medical treatment, visits to a specialized physician and nursing care. The intervention costs of high-grade hospitals will be compared to those of CHCs. Medicare national fee structures will be used to evaluate the costs of these services since out-of-pocket expenses for these services often do not accurately reflect the service value. Finally, the number of workdays lost by participants during rehabilitation will be used to assess indirect costs.

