**Method/design:**

This will be a randomized controlled clinical trial with blinded assessment. There will be a 4-week intervention utilizing rehabilitation protocols from traditional Chinese medicine and conventional therapy. Follow-up will be conducted for a period of 12 weeks. A total of 722 participants with knee osteoarthritis will be recruited. Participants will be randomly divided into two groups: experimental and control. Primary outcomes will include range of motion, girth measurement, the visual analogue scale, and results from the manual muscle, six-minute walking and stair-climbing tests. Secondary outcomes will include average daily consumption of pain medication, ability to perform daily tasks and health-related quality-of-life assessments. Other outcomes will include rate of adverse events and economic effects. Relative cost-effectiveness will be determined from health service usage and outcome data.

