## Methods/design

### Study design

This will be a cluster randomized controlled trial with blinded assessment (Figure 1). The trial will comprise a 4-week intervention, using the CTCMRP and conventional therapy (CT), and a 12-week follow-up period. The protocol will be conducted at CHCs run by the Affiliated People’s Hospital of Fujian University of Traditional Chinese Medicine (Fujian province, China), the Comprehensive Traditional and Western Medicine Hospital of Guangdong province (Guangdong province, China), the Chengdu Military Region General Hospital of the Chinese People’s Liberation Army (Sichuan province, China) and the First Affiliated Hospital of Guangzhou University of Traditional Chinese Medicine (Guangdong province, China). To include a broad range of patients, this protocol includes CHCs in different areas. Fujian University of Traditional Chinese Medicine (FJTCM) is responsible for training and supervising rehabilitation therapists at all clinical sites. The evidence-based medicine center, which will be used for documentation and data analysis, is an independent site that performs data monitoring, randomization and statistical evaluation and will be blind to the intervention. Patients will be recruited through CHC outpatient clinics. The Human Research Ethics Committee at Fujian University of Traditional Chinese Medicine (Fujian province, China) approved the study.

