### Recruitment

Outpatients with KOA will be recruited from participating CHCs in China. All participants will be selected according to the above inclusion and exclusion criteria. Baseline measurements will include the general and demographic data for the subjects, assessment of the knee prior to testing, medication use, previous treatments, KOA complications and duration of KOA symptoms. Due to ethical considerations, non-steroidal, anti-inflammatory drugs will be permitted (and registered) as required for patients with visual analogue scale (VAS) scores over 5. All patients will be asked to refrain from seeking other forms of treatment during the trial. During the follow-up period, patients will be asked to report whether they have received other forms of treatment.

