### Interventions

The participants in the experimental group will undergo CTCMRP rehabilitation treatment. This consists of Chinese medical herb fumigation-washing, traditional exercises (developed from simplified t’ai chi and *yi jinjing*), acupuncture and *tuina*. Patients in the control group will undergo CT rehabilitation including physical factor therapy and kinesitherapy. The duration of rehabilitation will be 4 weeks, which is a common duration in clinical practice. During the rehabilitation period the therapist will monitor proper performance, exercise intensity and will progress the exercises, if necessary.

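### The only cost comparison stated is high-grade hospitals against CHCs, not CTCMRP against CT, and service costs and lost workdays stop at week 4 while outcomes continue

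*Protocol article*

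**What the plan says.** In the protocol article, the Method/design part of the abstract makes the economic promise: "Relative cost-effectiveness will be determined from health service usage and outcome data". The Statistical analysis section names a cost-effectiveness analysis but gives no comparator or time horizon for it.

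The Economic evaluation section gives the content:

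- Comparison: "The intervention costs of high-grade hospitals will be compared to those of CHCs". No other cost contrast appears there.
- Direct costs: "The cost of interventions will be assessed during the rehabilitation period". The items listed are hospital stay, emergency visits, general treatment, specialist visits and nursing care, valued with national fee structures.
- Indirect costs: "the number of workdays lost by participants during rehabilitation will be used to assess indirect costs".

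The Interventions section fixes the length of that period: "The duration of rehabilitation will be 4 weeks, which is a common duration in clinical practice".

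On setting, the Study design section says "The protocol will be conducted at CHCs run by" four named hospitals, and the Recruitment section says "Outpatients with KOA will be recruited from participating CHCs in China". The randomised groups are CTCMRP and CT (Randomization and allocation; Interventions).

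During the 12-week follow-up, "trained personnel will contact the participants each week via telephone". The calls ask about other treatments. Clinic visits at 6 and 12 weeks record the clinical outcomes and medication use (Follow-up).

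**The concern.** A cost-effectiveness statement needs a difference in cost and a difference in effect between the same two groups over the same period. The Economic evaluation section departs from this in two ways.

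First, the groups in the stated cost contrast are settings, whereas the groups for which the trial measures an effect are treatments. A hospital-against-CHC difference says nothing about what CTCMRP costs relative to CT, because both are given in CHCs.

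Second, the costing stops when treatment stops, while effects continue to be measured. The Discussion makes persistence of benefit during follow-up one of the trial's questions. If a 12-week effect were paired with a 4-week cost, later specialist visits, admissions or lost workdays would be missing from one side of the balance only.

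At stake is the economic conclusion that the Discussion announces, namely that the assessment will support the cost-effectiveness of the treatments. The clinical efficacy conclusions are not affected.

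**Working it through.** The plan gives no economic figure to reproduce, so the check compares what the promise requires with what the text states, followed by simple arithmetic on the time window.

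**1. The contrast.** Relative cost-effectiveness of the randomised treatments rests on

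(C_CTCMRP − C_CT) set against (E_CTCMRP − E_CT).

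| Quantity | Stated in the article? | Where |
|---|---|---|
| E_CTCMRP − E_CT | Yes: outcomes compared between groups | Statistical analysis |
| C_CTCMRP − C_CT | Not stated as a comparison | – |
| C_hospital − C_CHC | Yes | Economic evaluation |
| E_hospital − E_CHC | Not available: no hospital arm | Study design; Recruitment |

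The stated cost difference has no matching effect difference, and the measured effect difference has no stated cost difference.

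**2. Could the between-arm cost difference still be obtained?** In part. The service-use items and lost workdays are collected on participants, and nothing limits them to one arm. Outcomes are also assessed at 4 weeks (Timelines; Statistical analysis). A 4-week CTCMRP-against-CT cost comparison is therefore feasible from the planned data, though not stated.

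**3. The window.** Costed time is 4 weeks (Interventions). The observed time can be read in two ways:

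- Last assessment 12 weeks after baseline (Timelines): uncosted time = 12 − 4 = 8 weeks, which is 8/12 = 67%. Costed: 4/12 = 33%.
- 12-week follow-up after the 4-week intervention (Study design): total = 4 + 12 = 16 weeks; uncosted time = 16 − 4 = 12 weeks, which is 12/16 = 75%. Costed: 4/16 = 25%.

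**4. Is the limit just loose wording for the whole study?** This is unlikely. The Safety assessments section mentions the follow-up period explicitly when it means to include it. The Economic evaluation section refers to rehabilitation for both direct and indirect costs and does not mention follow-up.

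**5. What follow-up already records.**

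| Item | Recorded in follow-up? | Listed for costing? |
|---|---|---|
| Other treatments received | Yes, calls | No |
| Medication use | Yes, clinic visits | No |
| Hospital, emergency and specialist use, nursing care | Not stated | Rehabilitation period only |
| Lost workdays | Not stated | Rehabilitation period only |

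The gap therefore has two parts: items not collected after treatment, and items collected but not costed.

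**The case against.** The strongest reply has four parts.

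*An article condenses the full protocol.* Comparator, horizon and effect measure are often left to a longer document, and the abstract's promise in a two-group trial implies a between-arm analysis. This would answer a complaint about missing detail. It does not answer a comparator and a time window that the article does state and that do not match its own design.

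*The hospital comparison has a purpose.* The Background presents rehabilitation as concentrated in high-grade hospitals at high cost, and the Discussion argues that moving care to a CHC or home would lower the patient's burden. That argument is about setting, and a setting cost comparison bears on it. This stands: the comparison is legitimate as description, and the article never calls it randomised. It does not supply the cost of CTCMRP relative to CT.

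*The data allow an arm comparison.* A reader might infer that the trial cannot give relative cost-effectiveness at all. The documents do not support that: participant-level service use and lost workdays could give a 4-week comparison, and the treatment delivered under the protocol falls within those 4 weeks. Paired with 4-week effects, such an analysis would be narrow but coherent.

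*Later costs are not all lost.* A reader might also infer that everything after week 4 goes unrecorded. That is too strong, because other treatments and medication use are recorded in follow-up. They are simply not listed for costing.

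**Conclusion.** The point holds in a limited form. As written, the economic section fixes a contrast that is not the randomised one, and a cost window shorter than the outcome window, so it does not deliver the comparison the abstract promises. A 4-week CTCMRP-against-CT comparison remains possible but is not stated, and it would omit later service use and lost workdays.

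The uncosted time is 8 weeks if the last visit is 12 weeks after baseline, or 12 weeks if follow-up starts after treatment. It is tempting to read 67% to 75% as the share of cost missed or as a degree of bias. The documents do not support that: they give no follow-up costs, so neither the size nor the direction of any distortion can be stated.

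The conclusion assumes that the rehabilitation period in the Economic evaluation section is the 4 weeks given under Interventions, and that both arms are treated at the CHCs, as Study design and Recruitment indicate. Cost is listed under other outcomes in Table 6, so this should be corrected, but it does not touch the primary clinical analysis.

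**What to change.** 1. State CTCMRP against CT as the main economic contrast, with cost and effect over the same period as the clinical outcomes, and an analysis that allows for clustering by CHC.
2. Add questions on service use and lost workdays to the existing weekly calls and follow-up visits.
3. Cost the data on other treatments and medication that those contacts already collect.
4. Say whether the 12 weeks run from baseline or from the end of treatment, so that the cost period is defined.
5. Keep the hospital-against-CHC cost comparison as a supplement labelled descriptive and non-randomised, and do not use it to support a claim about CTCMRP relative to CT.

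The cost is a few extra questions, slightly longer calls and some plan wording. Recruitment was ongoing at publication, so follow-up cost data may be incomplete for participants already enrolled. That should be reported, with the 4-week comparison shown alongside. The change of contrast can be made for all participants.
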